^ Therefore, in states like Kerala which has the highest burden of NCDs, progress in the control of tobacco control needs sustainable solutions embedded in the community. Due to high occupancy rates in all-purpose rooms in slums, smoking within homes can result in a high level of SHS exposure. Hence, the high population density is not only a risk factor but also an opportunity to efficiently reach a vulnerable proportion of the population.
^
24
^

Community embedded networks such as the “Kudumbashree” (which means welfare of the family) is a community network of women in the State of Kerala working in close coordination with the local self- government.
^
25
^ Throughout the world, diverse community leaders and organizations has been explored,
^
26
^
^–^
^
28
^ which were feasible with varying degrees of effectiveness. Moreover, a study on a community-based intervention by women’s self-help group members showed a significant reduction in blood pressure levels among people living in urban slums of Kerala, India.
^
29
^ Also, our initial experience from a smoke free initiative as part of ‘Quit Tobacco international activities’ suggests that “tobacco smoke free homes initiative” were feasible and a six week campaign with self-help group members brought a 30% decline in second hand smoking in a vulnerable fisherman community.
^
30
^ Therefore, intuitively, the potential impact of such interventions on reduction in second hand exposure and improvement of cardiovascular and respiratory health is large. It can also have tangible and intangible social and economic benefits. Hence this study plans to examine the effectiveness of an intervention partnering the self-help groups in reducing the second hand smoke exposure within homes.

Outcomes of the intervention need to measure exposure to second hand smoke. Biomarkers and indicators of environmental pollution were considered. Urinary cotinine level is a widely used biomarker and has a good correlation with daily tobacco consumption and second hand exposure.
^
31
^ Urine cotinine concentrations are more sensitive than in blood or saliva, making urine a sensitive matrix to detect low-concentration exposure.
^
32
^ Indoor particulate matter (PM), despite a background concentration of respirable particulate matter (PM) due to cooking and infiltration from outdoors, is considered a good indicator of SHS, at relatively high levels.
^
28
^
^,^
^
33

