^ PM < 10 μm enter the respiratory tract, but may be the result of mechanical processes such as construction activities, road dust resuspension and wind whereas PM < 2.5 μm (fine particles) originate primarily from combustion sources such as smoking.
^
34
^ Quit rates and harm reduction are also outcomes which can be used to determine the impact of the intervention and will be reported as has been observed in other studies.
^
35
^
^,^
^
36
^

In order to assess the impact of the intervention on smokers perse FEV1/FEV6 was measured. This measure is a substitute for FEV1/FVC in diagnosing airflow obstruction and may better predict COPD-related pathology and morbidity.
^
37
^ The use of 6-s expiratory maneuvers makes handheld spirometry faster and easier, provides a more explicit end-of-test definition. Its use in primary care has also been demonstrated for the detection of COPD in adults.
^
38
^

Our intention is to enhance the application of evidence in the naturally occurring clusters which are the slums. Each of the slums is a unit with similar sociodemographic features where interventions can be more effective, compliance will be better and contamination less likely. We would like to capture the population level effects of the intervention. Thus, a cluster randomisation trial was chosen.

This study aims to assess the effectiveness of a “smoke-free home” intervention in partnership with women’s self-help groups in the slums of Kochi corporation, Kerala. This is a hybrid type 2 effectiveness-implementation research
^
39
^ combining the evaluation of effectiveness of the intervention and also assessing the implementation process. We hypothesize that a tobacco smoke-free home initiative in partnership with self-help group women will be effective in significantly reducing SHS in homes and SHS exposure among women and children of those homes over a period of 1 year. The specific aims are:
•To determine the effectiveness of an intervention led by women’s self-help groups to reduce indoor tobacco smoking by measuring urinary cotinine levels and reduction in indoor smoking by measuring PM 2.5 as an indicator for tobacco smoke in the home environment.•To correlate the urinary cotinine levels with the PM 2.5 in the indoor home environment.•To measure the effect of the intervention on the FeV1/FeV6 among smokers.•To explore the impact of the intervention on quitting rate, smoking intensity through in depth interviews and focus group discussions.

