*Data collection*: Four semi-structured questionnaires have been developed and pretested. They include household, smoker, spouse and child questionnaires. The household questionnaire is for the household and comprises sociodemographic variables, number of family members, identifying the smokers, number of rooms, ventilation, distance from the road, type of road, any other source of air pollution within 500 m, organic and inorganic waste disposal, cooking fuel used, ventilation in the kitchen, use of mosquito coils, incense sticks, and the presence of pet animals. The smokers’ questionnaire will determine smoking habits, age of initiation of smoking, types of tobacco product used, money spent on tobacco per week, quit attempts, frequency and place of smoking within home, smoking when children are around, nicotine dependence score, awareness of harmful effects of second hand smoke, and who influences smokers the most. Nicotine dependence has been assessed by the Fagenstrom scale. The spouse questionnaire will consist of exposure to second hand smoke at home, practice of indoor smoking, ventilation in the kitchen, exposure to second hand smoke outside the home, cleaning habits, cooking practices, and medication use. The child questionnaire will consist of domains on reports of second-hand exposure at home and outside, history of respiratory morbidity in the past 6 months and history of hospital admission. For older children above 12 years the domains will also consist of history of tobacco use, age of initiation, and awareness regarding harm of second hand smoke. Standard methods of measurement of weight and height will be taken of the smoker, spouse and child. Blood pressure of the smoker and spouse will be measured by an electronic sphygmomanometer in a seated position after ensuring that the person is relaxed. If the reading is ≥140/90 mmHg the measurement will be repeated after 30 min and the average of the two will be taken. In order to measure FeV1/FeV6 the smokers will be instructed to take a deep breath and blow hard and long (6 seconds) till a beep is heard. The mouth should be sealed around the disposable mouthpiece. The measurement will be noted down by the health worker. We will also measure SHS through the air pollution monitor within the home which will measure particulate matter of size 2.5 microns and is a marker for the presence of SHS in the home. The device will be charged and left in the home for recording for 6-8 hours at an elevated place. The machine will record PM 2.5, 10 PM. The sensor will record the readings every 5 minutes and the output will be in the form of a graph. After downloading in the evening it will be given in the next house. This will be done at 6, 10, and 16 months respectively (

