**Figure 1. f1:**
[figure not shown]
Flow diagram for recruitment and follow up.

The training booklet (6-8 pages) has been developed for the ready reference of the SHG women who will deliver the intervention. The training booklet has been prepared by a team comprising a sociologist, health educator, communication specialist, community medicine expert, ASHA, and two SHG workers. The training booklet will be in an easy to understand form. The training booklet will consist of a review of the burden of the problem of tobacco, particularly smoking, the problem of second hand smoke, impact on women and children, and the use of the 3 A’s in the local language. They will also contain advice on the importance of not smoking within the home. The SHG/kudumbasree members will be partners in the development of communication material and will assist in the development of a poster, leaflet, and flip chart in order to ensure clarity, relevance, easy readability and understanding.

In the intervention clusters, an air quality monitoring committee will be formed to support the intervention. This will comprise of the SHG, ASHA, junior public health nurse (female health worker), ward councillor, and members of our team. This committee will guide the intervention. In the initial two months of the intervention the SHG-ASHA team will conduct monthly home visits for educating the smoker, spouse and others in the family on the harms of second-hand smoke using a flip chart. The circle of influencers around the smoking men will also be contacted by the members of the self-help group to provide support to quit. They will then organize a meeting of community leaders and heads of women’s groups, present data on harms of SHS, explain the rationale for establishing smoke free homes in their community, and ask for their assistance in arranging other educational meetings for community members. Two-three such educational meetings will be conducted per cluster where all the household members, particularly that of the smoking households, are encouraged to attend. These meetings will be conducted at different places in the community and doctors from the nearby primary health centres will come and talk about the harms of SHS and importance of becoming a smoke free home community. In these meetings other stakeholders, formal and informal leaders of the community, and local self- government representatives will be invited.

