In the next two months home visits will be conducted to paste the smoke free home stickers or distribute the calendars and reinforce the message of not smoking within homes and to get widespread recognition of the movement. Based on the findings of the baseline survey customized messages to quit will be delivered. The SHG-ASHA combined will also communicate the results of the cotinine levels and 2.5pm to the household members. The cotinine levels among the children and women will be an especially powerful tool to motivate and influence men to quit smoking within the homes and then to quit ultimately. If they express an interest to quit, they will be referred to the nearest urban primary health center for tobacco cessation. The influencers will be contacted again to encourage the smoker to quit smoking within home and to quit. Creating a movement and making “not smoking within the house an acceptable sociocultural norm” is the objective. At the end of the intervention as part of the dissemination activity smoke free homes declaration meeting for all community members in the presence of political leaders will be conducted.

*Control arm*: The other arm will get the standard of care which would include the routine programs which are being run by the government as part of the national tobacco control program such as training of health and social workers, NGOs, school teachers, and enforcement officers; Information, Education, and Communication (IEC) activities; school programmes; monitoring of tobacco control laws; coordination with Panchayath Raj Institutions for village level activities; and setting-up and strengthening of cessation facilities including provision of pharmacological treatment facilities at district level. Periodic assessments will be done at 10 and 16 months.

Health workers will conduct end-line surveys soon after the intervention and six months after the intervention in the intervention and control arm with the same questionnaire, urinary cotinine measurement and SHS measurement with an environmental sensor. Thus the measurements will be at 6, 10 months and 16 months respectively.

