•To correlate the urinary cotinine levels with the second-hand smoke in the home environment: correlation and linear regression analysis will be carried out by Pearson’s correlation if it follows a normal distribution and Spearman if it is a non-normal distribution.The difference in cotinine levels will be analysed by comparing the urine level of cotinine at the end of follow up, adjusted for the baseline value, by using linear mixed model or GEE to allow for cluster effect.•To measure the effectiveness of the intervention among smokers by measuring their FeV1/FeV6 using COPD6.To determine the effectiveness of the intervention in improvement of lung function the ratio of FeV1/FeV6 will be measured pre- and post-intervention and the mean difference between the groups will be assessed by a paired t-test.
**
*Qualitative data analysis*
**

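### Total indoor PM2.5 is read as second-hand smoke, and PM2.5 feedback is described only for the intervention arm, so a PM2.5 difference between arms may partly reflect other sources

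*Protocol article*

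**What the plan says.** Three places in the protocol article equate PM2.5 with tobacco smoke. Under Participants (data collection): "We will also measure SHS through the air pollution monitor within the home", a device said to measure "particulate matter of size 2.5 microns and is a marker for the presence of SHS in the home". The first specific aim, at the end of the Introduction, assesses reduced indoor smoking "by measuring PM 2.5 as an indicator for tobacco smoke in the home environment". The statistical plan under Outcomes restates the correlation aim as "To correlate the urinary cotinine levels with the second-hand smoke in the home environment", whereas the Introduction states the same aim in terms of PM2.5.

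The Introduction also qualifies this reading. It calls indoor particulate matter a good indicator of second-hand smoke "despite a background concentration of respirable particulate matter (PM) due to cooking and infiltration from outdoors", and only when levels are fairly high. The household questionnaire covers cooking fuel, kitchen ventilation, mosquito coils and incense.

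On the arms, the Intervention section has the field team "communicate the results of the cotinine levels and 2.5pm to the household members". It also says: "In the intervention clusters, an air quality monitoring committee will be formed to support the intervention". The control arm is described as receiving routine government programmes and the periodic assessments, with no feedback of results.

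PM2.5 is a secondary outcome; the primary outcome is urine cotinine. The stated adjustment covers individual covariates and factors found unbalanced at baseline.

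**The concern.** An outcome that responds to several sources is given the name of one of them, and its value is fed back to one arm only. A household shown a high PM2.5 reading has a reason to burn less incense, use fewer coils or change how it cooks. Any of these lowers the next reading without a change in smoking.

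Ventilation needs separate treatment. Opening windows dilutes tobacco smoke as well, so it can lower true exposure. It misleads only when lower PM2.5 is read as less indoor smoking, which is how the first aim uses it.

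At stake are the secondary PM2.5 comparison, the PM2.5 half of the first aim, and the cotinine-PM2.5 association. Incense, coil and cooking particles carry no cotinine, so they do not bias the primary outcome, but they weaken its association with PM2.5.

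**Working it through.** **The plan's own figure.** The Sample size section gives ICC 0.06, mean cluster size 20, CV 0.45, VIF 2.4 and 113 per arm before clustering.
- VIF = 1 + ((CV² + 1)m − 1) × ICC = 1 + ((0.2025 + 1) × 20 − 1) × 0.06 = 1 + 23.05 × 0.06 = 2.383, stated as 2.4.
- 113 × 2.4 = 271.2, stated as 271; 271.2/20 = 13.6, so 14 clusters.
- With 10% dropout, 271/0.9 = 301 or 271 × 1.1 = 298, rounded to 300.

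The sample size reproduces and is not in dispute. The VIF is borrowed below.

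**Does the planned analysis deal with the problem?** The Introduction prefers PM2.5 to coarser particles because fine particles come mainly from combustion. Cooking, incense and coils are combustion too, so that argument does not single out tobacco. The rule to adjust for factors unbalanced at baseline cannot reach sources that change after randomisation, perhaps because of the intervention. The correlation analysis names no adjustment for sources.

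**Possible size.** The document gives no PM2.5 mean, SD, ICC or tobacco share. All three illustrations rest on assumed values.

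1. *Shift in the mean.* Fall in total PM2.5 = non-tobacco share × proportional cut in those sources. With an assumed 20% cut in intervention homes only:
   - share 25%: 0.25 × 0.20 = 5%
   - share 50%: 0.50 × 0.20 = 10%
   - share 75%: 0.75 × 0.20 = 15%

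2. *Chance of a significant PM2.5 difference with no tobacco effect.* Assume that VIF 2.4 also holds for PM2.5, with the planned 300 homes per arm. Effective n = 300/2.4 = 125 per arm, and the standard error of the difference is √(2/125) = 0.126 SD. For a non-tobacco shift of b SD in the intervention arm alone, the probability is Φ(b/0.126 − 1.96) + Φ(−b/0.126 − 1.96):
   - b = 0: 5%
   - b = 0.05: 7%
   - b = 0.1: 12%
   - b = 0.2: 35%
   - b = 0.3: 66%

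   At b = 0.2, a VIF of 1.6 gives 49% and a VIF of 3.5 gives 26%.

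3. *Cotinine-PM2.5 correlation.* If a fraction f of PM2.5 variance is unrelated to tobacco and to cotinine, the correlation is multiplied by √(1 − f):
   - f = 0.25: 0.87
   - f = 0.50: 0.71
   - f = 0.75: 0.50

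Illustrations 1 and 2 cannot be linked, because converting a percentage fall into SD units needs the missing PM2.5 mean and SD.

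**The case against.** The case against has real weight.

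- **Messages to households.** A reader might infer that intervention homes are told to cut other sources of smoke. The text does not say so. Results are communicated, and every household message described concerns tobacco. Indoor air pollution appears in staff training alongside tobacco law, and the committee exists to support the smoke-free intervention. This stands: the bias is a possibility that the design leaves open.
- **Source data.** Cooking fuel, ventilation, coils and incense are collected, and the end-line surveys reuse the questionnaire in both arms, so these items appear to be asked again. The article only summarises the forms, so whether they cover the monitored hours cannot be checked. Covariates for the PM2.5 model may properly be left to an analysis plan. This stands in part: adjustment for baseline values would still miss later changes.
- **Correlation aim.** A weaker correlation with total PM2.5 is an honest answer to the aim as the Introduction words it. This stands, but the analysis section calls the same variable second-hand smoke.
- **Replacing the outcome.** Removing intervals around logged sources might seem the natural new main outcome. It could add bias: the log would be self-reported in unblinded homes, it describes behaviour after randomisation, and tobacco smoked during cooking would be removed too. This stands, and the fix respects it.
- **Consequence.** The primary outcome is cotinine, and self-reported indoor smoking gives a further check. This stands and limits the importance of the point.

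**Conclusion.** The point holds for the PM2.5 outcome and its interpretation. The monitor measures all fine particles, the article labels the result as tobacco smoke while conceding other sources, and only the intervention arm is described as learning its readings. A between-arm difference in PM2.5 can be reported as a difference in total indoor PM2.5. It does not by itself show reduced second-hand smoke or less indoor smoking.

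The size is unknown. On the assumptions shown, a modest shift confined to one arm (0.1 to 0.3 SD) would raise the chance of a significant PM2.5 result with no tobacco effect from 5% to about 12% to 66%. These figures show what could happen; they do not estimate what will.

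A reader might infer that the trial's main conclusion is compromised, or that PM2.5 bias is certain. The document supports neither. Cotinine is unaffected by incense, coil or cooking particles, and no passage tells homes to change those sources. The change is worth making because it is cheap and alters what may be concluded from PM2.5, not because the primary analysis is at risk.

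**What to change.** 1. Keep total PM2.5 compared by randomised arm as the secondary outcome, but name it total indoor PM2.5 throughout, including in the first aim and the correlation objective.
2. State that reduced smoke exposure or reduced indoor smoking will not be concluded from PM2.5 alone, without agreement from cotinine and self-reported indoor smoking.
3. At the remaining recordings in both arms, have the worker who collects the monitor note cooking, incense, coil use, indoor smoking and open windows during those 6-8 hours. Report these by arm at 10 and 16 months.
4. Use PM2.5 with logged source intervals excluded, or adjusted for sources, only as a sensitivity analysis, and say that the log is self-reported and post-randomisation. One reading every 5 minutes gives 72 to 96 readings per run (360/5 to 480/5), so interval exclusion is feasible.
5. Report the cotinine-PM2.5 association both unadjusted and adjusted for recorded sources and ventilation.

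Cost: a few lines on a form at a visit already planned, and one or two derived variables. The downsides are recall error and, because baseline collection was already under way, no log for homes already measured.

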**Smoker**				
Smoking within homes (self-reports)		✓	✓	✓
Fagenstrom nicotine dependence score		✓	✓	✓
No of cigarettes smoked daily		✓	✓	✓
No of persons who have quit			✓	✓
Blood Pressure		✓	✓	✓
BMI		✓	✓	✓
Fev1/Fev6		✓	✓	✓
*Air pollution	PM 2.5	✓	✓	✓
	PM 10	✓	✓	✓
	CO _2_	✓	✓	✓
Women	Cotinine	✓	✓	✓
Child	Cotinine	✓	✓	✓
BMI	Child	✓	✓	✓
Resp. Infection	Child	✓	✓	✓
	Woman	✓	✓	✓
Process evaluation	In depth interview			✓
	FGD			✓

A door-to-door initial survey will be conducted following a training to the data collectors. After ascertaining the households where the male member smokes the interviews of the smoker, wife/close female relative, and child will be conducted. The interviews will be conducted separately for the husband and wife/close relative who is a woman. After the interview, Fev1/FeV6 ratio among the smokers will be assessed with the Vitalograph COPD-6 screener device. The women and child of the household will be asked to keep the urine sample in a sample bottle provided which is then placed in an auto seal pouch. These samples will be collected from all the houses and transported to the laboratory by maintaining cold chain at a temperature between 2-8 degrees C. The urinary cotinine levels among the women and children of the smoking households will be assessed in this urine sample. The cotinine levels will be assessed among the spouse of the smoker or among a woman who stays at home for a longer duration and a child up to 18 years of age. If there is more than one child in the house, the youngest child older than 1 year will be chosen. All houses may not have children; therefore, it is necessary to take both women and children’s cotinine levels. This would also be an important advocacy tool as the children’s cotinine levels can be used to influence the smoker. The urine cotinine level will be measured at 6, 10, and 16 months with the help of Cal biotech’s ELISA kit which will measure cotinine levels by ELISA (solid phase competitive ELISA). The test was calibrated and standardised in a pilot study among households of smokers and non-smokers and differences ascertained.

Quality of data collected will be ensured by training and retraining of the data collectors. The data collection forms are provided.
^
40
^
^,^
^
41
^ The laboratory tests will be carried out after validation. Data entry will be done with back up and range check-ups will be done for data values.

Frequent meetings of the data monitoring committee (DMC) will be carried out to minimise dropout. The members of local self-government will also be taken into confidence to minimise dropout. The data monitoring committee is independent of the sponsors and is situated locally and consists of external senior public health personnel, investigators, sociologists and data analysts. The data regarding unintended effects will also be collected.

